## Abstract

**Background:**

Almost 50% of Americans have elevated low-density lipoprotein cholesterol (LDL-C). The behaviors required to lower LDL-C levels may be difficult to adhere to if they are inconsistent with spouses' health practices, and, alternatively, may be enhanced by enlisting support from the spouse. This trial extends previous trials by requiring spouse enrollment, teaching spouses how to provide emotional and instrumental support, allowing patients to decide which component of the intervention they would like to receive, and having patients determine their own goals and action plans.

**Methods:**

Veteran outpatients with above-goal LDL-C (N = 250) and their spouses are randomized, as a couple, to receive printed education materials only or the materials plus an 11-month, nurse-delivered, telephone-based intervention. The intervention contains four modules: medication adherence, diet, exercise, and patient-physician communication. Patients decide which modules they complete and in which order; modules may be repeated or omitted. Telephone calls are to patients and spouses separately and occur monthly. During each patient telephone call, patients' progress is reviewed, and patients create goals and action plans for the upcoming month. During spouse telephone calls, which occur within one week of patient calls, spouses are informed of patients' goals and action plans and devise strategies to increase emotional and instrumental support.

The primary outcome is patients' LDL-C, measured at baseline, 6 months, and 11 months. Linear mixed models will be used to test the primary hypothesis that an 11-month, telephone-based patient-spouse intervention will result in a greater reduction in LDL-C as compared to printed education materials. Various process measures, including social support, self-efficacy, medication adherence, dietary behavior, and exercise, are also assessed to explain any change, or lack thereof, in LDL-C.

**Discussion:**

Given the social context in which self-management occurs, interventions that teach spouses to provide instrumental and emotional support may help patients initiate and adhere to behaviors that lower their LDL-C levels. Moreover, allowing patients to retain autonomy by deciding which behaviors they would like to change and how may improve adherence and clinical outcomes.

**Trial Registration:**

The ClinicalTrials.gov registration number is NCT00321789.

## 

Coronary heart disease (CHD) is the leading cause of death in the United States, resulting in more than 500,000 deaths and an additional 500,000 nonfatal heart attacks annually.[1,2] One major modifiable risk factor for CHD is elevated low-density lipoprotein cholesterol (LDL-C). Every 1% reduction in LDL-C is accompanied by a 1% reduction in individuals' short-term risk of a major coronary event.[2] Consequently, current guidelines designate LDL-C as the primary target of lipid-lowering therapy.[2] Despite the proven efficacy of lifestyle modifications and lipid-lowering medications, almost half of American adults have borderline high or high LDL-C, defined as 130 mg/dL or above.[2] Therefore, novel interventions are needed to lower LDL-C levels.

Patient interventions have proven effective for increasing adherence to behaviors that would lower LDL-C levels.[3,4] However, changes are typically short lived, with less healthy behaviors returning after brief periods of time. One reason for nonadherence is that recommended lifestyle behaviors may be inconsistent with those of one's social network members.[4,5] Moreover, patients may have difficulty adhering to dietary changes when they are not involved in cooking meals or grocery shopping.[6] What is needed, then, are interventions that can enhance the social support provided by spouses/significant others in order to help patients adhere better to treatment recommendations.

Several trials have shown that spouses can help patients lower their cholesterol.[7,8] However, these studies have some limitations. First, they have targeted a young population.[9] or women. [10,11] Thus, these studies do not generalize to the VA setting, which consists of primarily older males for whom the female spouse is the primary meal planner. Second, these studies have evaluated relatively short-term interventions (i.e., less than 6 months).[9,11] Third, previous studies have simply encouraged emotional support, rather than *teaching *spouses how to provide better emotional *and instrumental *support. [10,12] This is important because spouses may do things to decrease treatment adherence (e.g., nagging). Fourth, previous studies have not allowed patients to create their own goals and action plans (i.e., steps for achieving those goals). This is important because people who are not ready to make a behavior change – especially one imposed on them – are unlikely to be adherent.[13] Finally, these studies have targeted only one component of the treatment regimen at a time – either lifestyle changes or medication adherence.[9,12]

Our proposed intervention, the CouPLES trial, extends interventions tested in previous studies in several ways. We will: (1) target elderly male veterans, a group at increased risk for dyslipidemia and associated morbidity; (2) assess both short-term (6 months) and long-term (11 months) effects of the intervention; (3) employ a multi-component intervention that includes modules for medication, diet, exercise, and patient-physician communication – all important components of treatment for dyslipidemia; (4) have patients create goals and action plans for whichever behavior they would like to change; and (5) teach spouses strategies to provide support that can enhance patients' adherence to healthy behaviors. In this paper, we describe the study design, recruitment strategy, and analytical techniques of a clinical trial to test this state-of-the-art CouPLES intervention.

### Patient population and recruitment

Our study population consists of married veterans with above-goal LDL-C. According to current guidelines, a patient's LDL-C goal depends on the number of major risk factors and the estimated 10-year risk for CHD according to the Framingham risk score.[2] The three risk categories and corresponding LDL-C goals are shown in Table 1.

**Table 1 T1:** Risk categories and LDL-C (mg/dL) goal

Risk Category	LDL-C Goal
High: CHD and risk equivalents*	<100
Medium: No CHD, ≥ 2 risk factors**	<130
Low: No CHD, 0–1 risk factor	<160

LDL-C: low-density lipoprotein cholesterol. CHD: coronary heart disease.

*Risk equivalents: diabetes, clinical forms of atherosclerotic disease, and multiple risk factors that confer a 10-year risk for CHD > 20% according to the Framingham risk score. **Risk factors: hypertension (blood pressure ≥ 140/90 mmHg or on antihypertensive medication), cigarette smoking, high-density lipoprotein cholesterol < 40 mg/dL, age (men ≥ 45 years, women ≥ 55 years), and family history of premature coronary heart disease (present in male first degree relative < 55 years or female first degree relative < 65 years).

We identify potential participants via a three-step process (Figure 1). In Step 1, we use VA administrative databases to identify married patients who have had a primary care visit and a lipid profile with LDL-C >100 mg/dL in the previous 12 months. We chose a cutoff of 100 mg/dL because that is the lowest possible guideline-recommended LDL-C goal. We also use the databases to exclude patients who meet any of the exclusion criteria listed in Step 1 of Figure 1.

**Figure 1 F1:**
[figure not shown]
**Steps in identifying potentially eligible patients**.

In Step 2, patients who have an upcoming clinic appointment receive a recruitment letter, followed by a screening telephone call. Based on responses given during the screening telephone call, patients who meet any of the exclusion criteria listed Step 2 of Figure 1 are excluded. Patients passing Step 2 are scheduled for an in-person screening visit with a research assistant (RA). Spouses are also required to attend; in most cases, spouses have been able to come at the same time as patients. This may not be true in a younger population that is more likely to be employed and caring for young children.

In Step 3, self-reported data and laboratory results obtained during the screening visit, combined with medical record data, are used to count patients' risk factors and calculate their Framingham risk scores (see Figure 1, Step 3). This information is used to determine patients' risk categories, as defined in Table 1, and their individual LDL-C goals based on the risk categories. Patients with above-goal LDL-C are eligible for enrollment. Eligible couples are randomized, as a pair, to the intervention or control arm. The randomization is stratified on patient race (White and non-White) and risk category (collapsed from three categories to two – high and medium/low – due to the low prevalence of the low-risk category). This will allow us to test for differential effects of the intervention on different race and risk groups, which will inform future interventions.

The screening visit also serves as the baseline visit for eligible patients. At this visit, patients and spouses provide written informed consent, complete baseline measures, and receive printed educational materials. After the visit, the research nurse who delivers the CouPLES intervention places a telephone call to inform patients of their laboratory results, eligibility, and when eligible, randomization assignment. During this telephone call as well as the intervention telephone calls preceding follow-up assessments, the nurse instructs couples not to reveal their study assignment to the RA so that the RA will be blinded for outcome assessments. Each couple receives $40 for each of the three visits.

### CouPLES intervention

#### Overview

The CouPLES intervention takes place over 11 months (Figure 2). A research nurse delivers the CouPLES intervention because clinical knowledge and judgment are required (e.g., for issues with medications or comorbidities). Prior to enrollment, the nurse received didactic training from a clinical psychologist ([name]) on the basic principles of motivational interviewing, including asking open-ended questions, learning how to use reflective listening, and learning to identify and elicit change talk from a patient. The nurse also learned how and when to reinforce patients and to express optimism about their ability to change. The nurse received feedback on several practice intervention calls to both patients and spouses from [name] and [name] During the trial, 5% of calls are recorded and reviewed to assure intervention fidelity, and feedback is provided as necessary.

**Figure 2 F2:**
[figure not shown]
**Intervention flowchart**.

The research nurse conducts all intervention telephone calls with patients and spouses separately. During the month 1 telephone call, patients and spouses receive an educational module. During the month 2 telephone call, patients choose one of four topical modules and create corresponding goals and action plans. During subsequent monthly telephone calls, which occur every month except months 6 and 11 when outcomes are assessed, patients' progress is reviewed, and patients revise or create new goals and action plans for the same or a different module. During all spouse telephone calls, spouses are informed of patients' goals and action plans and are provided with strategies to provide better emotional and instrumental support to help increase patient adherence. For example, spouses may exercise with patients or prepare their lunch so that they do not have to eat at a restaurant.

#### Module content

At month 1, the nurse delivers an educational module that reviews the importance of blood cholesterol to health, treatments for dyslipidemia, and principles of self-management. In the spouse educational call, the nurse also reviews behavioral principles for providing instrumental and emotional social support. Although this information is provided in the printed materials distributed at baseline, the nurse reviews it to ensure that all intervention patients will receive the information, regardless of levels of health literacy, and so that the nurse can answer any questions or clarify the information. Below, we describe the content of each of the four topical modules and processes for delivery.

#### Diet

The educational materials include a handout on portion sizes and the National Heart, Lung, and Blood Institute's cookbook *Keep the Beat: Heart-Healthy Recipes*. We designed the diet module to be applicable regardless of whether the patient or spouse is the primary meal preparer in the home, and we provide different suggestions for people who do and do not cook. The nurse asks spouses if they plan to make the same dietary changes as the patients and provides appropriate suggestions.

#### Exercise

Patients receive a handout emphasizing the importance of exercise to health and suggesting ways to start an exercise program, stay motivated, deal with pain, and prevent overexertion. As in the diet module, the nurse asks spouses if they plan to exercise with patients and provides appropriate suggestions.

#### Medication adherence

This module will only be applicable to patients who are on lipid-lowering medications (which is not an inclusion criterion) and who need assistance to increase medication adherence. We provide information sheets on lipid-lowering medications that include dosages, dosing instructions, the most common side effects, and important warnings, all written at an eighth grade reading level. Suggestions to spouses correspond to patients' goals and may include ordering refills, encouraging patients to contact their pharmacist or physician about side effects, and helping patients prepare pill boxes.

#### Patient-physician communication

The written materials suggest ways patients can improve the quantity and quality of communication with their providers. The nurse provides practical suggestions for bringing concerns to the doctor's attention and encourages role-playing with spouses to increase patients' self-efficacy. The nurse also helps patients problem-solve and set goals that are reasonable to accomplish at their next clinic visit using methods such as role-playing.

#### Module delivery

During the initial patient telephone call, patients choose one of the four topics. The nurse asks open-ended questions about what they have tried in the past, what has worked, and what has not worked. The nurse also uses reflective listening to help patients establish possible goals related to the topic chosen. The nurse asks patients to rank each possible goal in order of importance to determine which goals will be pursued in the upcoming month. Next, the nurse uses open-ended questions to elicit from patients how they will attempt to make the behavior changes necessary to reach that month's goals and how to integrate the spouse in the plan; these specific behaviors are designated as action plans. For each action plan, patients are asked to rate their self-efficacy on a 1–10 scale (1 = *not at all confident*, 10 = *very confident*). Patients reporting < 7 are asked to revise their action plans and/or goals until ratings ≥ 7 are provided, as patients will be more likely to accomplish their goals.[14] Patients are asked to record that month's goals and action plans on provided goal sheets, which they can refer to anytime.

The follow-up patient calls take place 3–5 weeks after the initial calls (i.e., there is a 2-week window during which calls must occur, otherwise the call is skipped). During these calls, patients are asked whether they met their goals. Patients who met their goals are reinforced and encouraged to create additional goals and action plans. Patients who did not meet their goals are encouraged to modify their original goals and action plans or create new one(s).

All spouse calls occur within one week of the patient calls. During these calls, spouses are informed of whether patients indicated that they met their goals and about patients' new or revised goals and action plans. Spouses are encouraged to think of ways to help patients achieve their new or revised goals and, when necessary, are provided with suggestions.

This intervention takes into account patients' motivation to change specific behaviors by allowing them to determine which modules they receive and the order in which they receive them. This way, patients address the areas about which they are most motivated to make behavioral changes. Some patients may not wish to complete one or more modules. Because this is a patient-centered intervention, the protocol is flexible so that modules can be repeated or omitted.

#### Information technology for intervention delivery

Two customized database applications were created: one for the delivery of the CouPLES intervention, and one for the tracking of all related data. Once couples are randomized to the intervention, relevant information is automatically transferred from the study tracking database to the intervention application database to facilitate intervention delivery. This information includes participants' names, contact information, demographic data, and contact information for patients' VA primary care provider.

Once couples' information enters the intervention application database, the nurse can track the date on which the next telephone intervention call is due to both patients and spouses, as well as dates of previous intervention telephone calls. Several other important features of the application facilitate tracking of telephone calls. First, a calendar notes the patient-specified best days and times to be reached. This information is obtained by the nurse during the educational telephone call and allows calls to be made when the participant is most likely to be available. The application provides lists of all patients and spouses due for telephone calls and notes those who are currently available. Second, the application allows the nurse to document the number of missed calls, time periods when the participant will be on vacation or otherwise unavailable, and any other notes regarding availability. Third, the application automatically records the duration of each telephone call. This information will be used in the economic evaluation and will provide information regarding the time required to implement this type of intervention in a real-world clinical setting.

In addition to tracking telephone call schedules and data, the application facilitates implementation of the intervention. For each topical module, the application provides scripts for the nurse to follow during each telephone call. These scripts contain summary points, questions for patients and spouses, and suggested behaviors that patients and spouses could designate as action plans to follow over the next month (Figures 3 and 4 display dietary suggestions from the patient and spouse diet modules; names are fictitious). Most importantly, the application provides an interface for documenting and tracking patients' goals and action plans (Figure 5 displays goals and action plans for a fictitious patient). For a selected topic, all goals and action plans are displayed, and the software shows which goals are active, inactive, or complete at the time of the telephone call. The application also tracks patients' self-efficacy at the time action plans are initiated, and whether the goal was initiated by the participant or initially suggested by the nurse.

**Figure 3 F3:**
[figure not shown]
**Patient telephone script from diet application**.

**Figure 4 F4:**
[figure not shown]
**Spouse telephone script from diet application**.

**Figure 5 F5:**
[figure not shown]
**Patient goals from intervention delivery application**.

#### Study measures

Control variables are assessed at baseline. The primary, secondary, and process measures are assessed at baseline, 6 months, and 11 months.

#### Control variables

Demographic variables (age, sex, race, education, financial stress, employment status) and clinical variables (cholesterol medication use, frequency of cholesterol testing, alcohol and tobacco use, antihypertensive medication use, family history of CHD) are assessed at via self-report. Health literacy is assessed with the Short Test of Functional Health Literacy in Adults (S-TOFHLA).[15] Comorbidities are assessed with a self-report checklist.[16]

#### Primary outcome

LDL-C is measured directly using a non-fasting lipid profile. We chose a non-fasting test because it reduces patient burden and therefore may increase our enrollment rate. The blood sample is analyzed with an LXi from Beckman Coulter. The coefficient of variation for LDL-C ranges from 3.3 % at 106 mg/dL to 4.1 % at 49 mg/dL.

#### Secondary outcomes

Dietary behavior is assessed with the Block Brief 2000 Food Frequency Questionnaire (FFQ).[17] Exercise is assessed with the Community for Healthy Activities Model Program for Seniors (CHAMPS) questionnaire.[18] Medication adherence is assessed with the Med-Out index, which is calculated for each lipid-lowering medication.[19]

#### Process measures

Several measures are collected to determine what is responsible for LDL-C change. These include cholesterol knowledge; self-efficacy and outcome expectancies for each of the behaviors; spouse support for dietary change.[20] and exercise;[21] satisfaction with the dyadic relationship;[22] amount of patient-physician communication;[18] and intervention intensity (i.e., how many phone calls were completed).

### Sample size and statistical power

The primary hypothesis is:

(H1) An 11-month, telephone-based patient-spouse intervention will result in a greater reduction in LDL-C as compared to printed education materials.

In our sample size calculations, we assume no change for patients who receive only printed education materials and a 7% reduction in LDL-C (based on a 2-month pilot study using the same intervention materials) for intervention patients from baseline to 11 months. Based on a standard deviation adjusted to account for correlation between repeated measurements of the outcome, and using an independent samples t-test with a 0.05 two-sided significance level and 80% power, a sample size of 100 patients per group is required to detect a 9.4 point (7%) difference in change of LDL-C values between the intervention and control groups. Because we assume an approximate dropout rate of 20%, we will recruit approximately 125 couples per arm.

### Primary analyses

The unit of analysis is the patient. Because LDL-C, a continuous variable, is assessed at baseline, 6 months, and 11 months, we will use a linear mixed-effects model (LMM).[23] Fixed effects in the model will include intervention group, time, and the interaction between these two variables. This will enable us to determine the effects of the intervention at both 6 and 11 months. Patient-level random effects will be included in the model to account for correlations between patients' repeated measures over time. Primary analyses will be conducted as intent-to-treat, and sensitivity analyses will examine the implications of the intent-to-treat assumption.

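### The primary mixed model gives each arm its own baseline LDL-C mean; it is valid, but a common-baseline model would be more precise at almost no cost

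*Protocol article*

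**What the plan says.** The model is set out under Primary analyses in the protocol article. Baseline is one of the repeated outcomes: "Because LDL-C, a continuous variable, is assessed at baseline, 6 months, and 11 months, we will use a linear mixed-effects model (LMM"). The mean structure follows: "Fixed effects in the model will include intervention group, time, and the interaction between these two variables". The within-patient correlation is handled by random effects: "Patient-level random effects will be included in the model to account for correlations between patients' repeated measures over time". No constraint of equal baseline means is stated, and baseline LDL-C is not listed under Control variables.

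The timing of baseline is given under Patient population and recruitment: "The screening visit also serves as the baseline visit for eligible patients". Eligibility is decided from that visit's laboratory result ("Patients with above-goal LDL-C are eligible for enrollment"), and randomization follows ("Eligible couples are randomized, as a pair, to the intervention or control arm"). The nurse tells the couple their assignment by telephone after the visit. Before that, Step 1 of recruitment already requires an LDL-C above 100 mg/dL in the previous 12 months.

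Under Sample size and statistical power, the target is a 9.4-point (7%) between-arm difference in LDL-C change with 100 patients per arm, "using an independent samples t-test with a 0.05 two-sided significance level and 80% power". The SD is described only in words: "Based on a standard deviation adjusted to account for correlation between repeated measurements of the outcome".

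**The concern.** A group main effect in a model that also contains the baseline value as an outcome lets the two arms differ at baseline. In a randomized trial with a pre-randomization baseline, the true baseline means are equal, so that parameter estimates only chance. Spending a parameter on it turns the month-11 interaction into a comparison of changes from baseline, which subtracts the whole baseline value even though follow-up regresses on baseline with a slope below 1. The chance difference at baseline is then over-corrected and adds noise to the treatment estimate.

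What is at stake is precision: a wider confidence interval and a lower chance of detecting the 9.4-point target than the same patients and the same blood samples could give.

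**Working it through.** **Inputs from the article.** Difference 9.4 mg/dL, 100 completers per arm, two-sided 0.05, 80% power, 20% dropout, 1:1 allocation. **Inputs not given, so assumed.** Correlation ρ between visits, and the LDL-C mean and SD.

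**1. Reproduce the plan's figure.** The SD is not stated, so it can only be solved for. By the normal formula, SD = 9.4 / [(1.960 + 0.842) × √(2/100)] = 23.7 mg/dL; with the noncentral t it is 23.6. Putting 23.7 back gives 100 per arm. Dropout: 100 / 0.80 = 125, as stated. The implied baseline mean is 9.4 / 0.07 = 134 mg/dL.

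**2. Variance of the month-11 contrast, complete data, equal variance σ² at each visit, n per arm.**
- Planned model (free baseline means): 2(1−ρ)σ² × 2/n
- Common baseline mean: (1−ρ²)σ² × 2/n
- Ratio: (1−ρ²) / [2(1−ρ)] = (1+ρ)/2, below 1 for every ρ < 1

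**3. Without truncation, SD of change held at 23.7 and 100 completers per arm (planned SE 3.36, power 80%).**

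| ρ | Ratio | SE, common baseline | Power | n per arm for 80% |
|---|---|---|---|---|
| 0.5 | 0.75 | 2.91 | 90% | 75 |
| 0.7 | 0.85 | 3.09 | 86% | 85 |
| 0.9 | 0.95 | 3.27 | 82% | 95 |

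With 125 recruited and 20% dropout (half before month 6, half before month 11) the ratios become 0.79, 0.87 and 0.96. The planned model then borrows from month 6 and is no longer exactly a completers' change score, but it remains the less precise of the two.

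**4. With the entry rule.** The table above is too favourable, because patients enter on high LDL-C, which narrows the baseline distribution. I simulated a multivariate normal clinic population (mean 105–125, SD 30–35, ρ 0.6 or 0.8 between all visits) and kept patients with LDL-C above 100.

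| Selection | Slope of follow-up on baseline | Variance ratio |
|---|---|---|
| Above 100 at both Step 1 and baseline | 0.51–0.75 | 0.84–0.91 |
| Above 100 at baseline only | 0.60 (ρ=0.6), 0.80 (ρ=0.8) | 0.87–0.91 (ρ=0.6), 0.94–0.96 (ρ=0.8) |

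With both steps, the simulated baseline means are 129–142 mg/dL, which brackets the implied 134.

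**5. Translate to power.** The planned 80% corresponds to a standardized effect of 1.960 + 0.842 = 2.80.
- Ratio 0.84: 2.80/√0.84 − 1.96 = 1.10, power 86%; equivalent completers 200/0.84 = 238
- Ratio 0.91: 2.80/√0.91 − 1.96 = 0.98, power 84%; equivalent completers 200/0.91 = 220
- Ratio 0.94: 2.80/√0.94 − 1.96 = 0.93, power 82%

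**6. Check that the remedy's SE is honest.** With baseline truncated at 100 (mean 125, SD 30, ρ=0.4), a common-baseline model with only a random intercept reported a mean SE of 3.61 against an empirical SD of 3.94. Adjusting the follow-up value for baseline by regression, which with complete data matches the common-baseline model with unstructured covariance, gave 3.89 against 3.97. The average estimate was close to the true 9.4 for the planned model and both alternatives.

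**The case against.** The strongest reply is that nothing here is inconsistent. The hypothesis concerns a greater reduction, the sample size is built on a difference in change, and the interaction term estimates exactly that. The analysis has the right type I error and is unbiased. The article is also condensed: its list of fixed effects omits the stratification factors too, so a fuller document may adjust for baseline. All of this stands except the last step. The article does specify the mean structure, and nothing in it points to a common baseline or a baseline covariate.

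It is also fair that the gain rests on values the article does not give, and that truncating baseline shrinks it. Results such as 90% power at ρ=0.5 ignore the entry rule and should not be used as the headline.

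Three stronger readings are tempting and not supported:

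- A reader might infer that the trial is underpowered, by taking the adjusted SD to be a covariance-adjusted one, σ√(1−ρ²), which the planned model would not achieve. The wording does not strictly exclude this, but the article describes a t-test on a difference in change, so the natural reading is the SD of change. On that reading the planned model has its 80%.
- A reader might infer bias, because a chance baseline imbalance passes into the estimate with the opposite sign. That error is conditional on the observed imbalance and averages to zero over randomizations. It is the same imprecision as in the variance ratio, not a second defect.
- A reader might infer that selection on the baseline visit itself pulls the slope below 1. It does not: the slope stayed at ρ under baseline-only truncation. It is below 1 because ρ is below 1, and the earlier Step 1 selection lowers it further.

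**Conclusion.** The point holds as a loss of efficiency in a valid analysis. For assumed ρ of 0.6–0.8 and entry above 100 mg/dL at both steps, the planned model's variance could be cut by about 9–16%. That is worth about 84–86% power instead of 80% at 100 completers per arm, or the information of 220–238 completers from 200. If ρ is higher, or if only the baseline value is effectively truncated, the gain can shrink to about two points (82%). The direction is certain for any ρ below 1; the size depends on the assumed ρ and LDL-C distribution and on a single threshold of 100 at each step, whereas the individual goals are 100, 130 or 160. The change is worth making because it is almost free, not because the planned analysis would mislead.

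**What to change.** Before outcome data are analysed, restate the primary model as follows: time as a categorical factor, one baseline mean common to both arms (no group main effect at baseline), group-by-6-month and group-by-11-month terms, and an unstructured 3×3 covariance across the three visits. The primary estimate is the group-by-11-month term.

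The covariance change belongs with the constraint: with a random intercept alone, the common-baseline model can understate its SE when baseline is truncated by the entry rule.

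An alternative is to model the 6- and 11-month LDL-C only, with baseline LDL-C and its interaction with time as covariates.

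The cost is a sentence or two of analysis wording. No new data, visits or patients are needed, and the planned 125 couples per arm can stand.
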